## Abstract

**Background:**

Aortic stenosis is the most common valvulopathy in Western countries. The treatment of choice had been surgery aortic valve replacement (SAVR), but the improvement in endovascular approaches as transcatheter aortic valve implantation (TAVI), initially reserved for patients with very high surgical risk, has been extended to high and intermediate, and recently also to low-risk patients. Stroke and vascular cognitive impairment are the most important complications. It is not entirely clear which technique is best to avoid these complications as well as their impact. Our goal is to evaluate changes in cognitive performance in the early (1-month) and late (1-year) postoperative period in patients undergoing SAVR or TAVI, by extensive neuropsychological study (NRP) and advanced Magnetic Resonance Imaging (MRI).

Specifically, to compare early and late cognitive changes after the intervention between both groups, the occurrence of stroke during follow-up and to compare the appearance of silent vascular lesions and changes in brain activity and functional connectivity with functional MRI during follow-up between both groups.

**Methods/design:**

Prospective longitudinal cohort study. A non-selected representative sample of 80 subjects, 40 SAVR and 40 TAVI to obtain a final sample of 36 eligible subjects in each group, ranging from 70 to 85 years old, with indication for aortic replacement and intermediate or high surgical risk will be studied. At baseline, within one month before the treatment, all individuals will undergo an extensive NRP and advanced MRI study. These studies will also be performed 1-month and 1-year after treatment, to assess the appearance of new vascular lesions, as well as changes in cognitive performance with respect to baseline.

**Discussion:**

This study aims to evaluate changes in cognitive performance as well as both clinical and silent vascular events occurring in the early (1-month) and late (1-year) periods after SAVR and TAVI. We will also analyze the correlation between neuropsychological and neuroimaging approaches in order to evaluate cognition. Therefore, it may provide high-quality data of cognitive changes and vascular events for both techniques, and be useful to tailor interventions to individual characteristics and ultimately aiding in decision-making.

**Trial registration:**

This study is register in Clinicaltrials.gov (NCT05235529) on 11^th^ February 2022.

## Background

Degenerative aortic stenosis (AS) is the most common valve heart disease among older patients in developed countries, with an exponential increase in prevalence with age. A meta-analysis conducted in those countries found a population prevalence of AS and severe AS in those aged 75 years and older of 12.4% and 3.4% respectively [1, 2].

Surgical aortic valve replacement (SAVR) has been the treatment of choice for patients with severe AS, but it is not appropriate for high-risk patients. In this scenario, over the past decade, several randomized controlled trials and observational studies have established the non-inferiority and even superiority of transcatheter aortic valve implantation (TAVI) compared with SAVR in high-risk patients or those considered inoperable [3–6].

Improvement in the learning curves of the endovascular technique, in the devices, and in the access routes have led to the indication of TAVI in intermediate-risk patients [7–9]. For this reason, nowadays-international guidelines have recommended the use of TAVI in inoperable and high-risk patients (Class I) and in intermediate-risk patients (Class IIa) [10–12].

Previous results and the minimally invasive technique of the TAVI procedure have encouraged investigations, as the recently published PARTNER 3 and Evolut Low-Risk trials [13, 14], showing non-inferiority and even superiority of TAVI compared with SAVR for some of the outcomes in low-risk patients.

Mortality and postoperative complications in patients undergoing aortic valve replacement are variable. In this study, we will focus on the most important and potentially disabling cerebral vascular events and vascular cognitive impairment (VCI).

In 2010 the PARTNER randomized trial showed a significant increase in stroke in the TAVI group compared with SAVR (5.5% and 2.4%) [4]. Two meta-analyses published in 2013 [15, 16] did not show significant differences (3.5 vs. 2.8% and 2.6 vs. 2.3%). Although the rate of stroke may have decreased marginally as TAVI has improved, questions continue to arise about the importance of microembolisms or silent cerebral infarcts that may cause changes in cognition. TAVI is associated with a high incidence (up to 84%) of silent cerebral embolism as detected by diffusion-weighted MRI (DW MRI) [17], more frequent than that following aortic valve surgery [18]. However, a clear correlation between the number or volume of vascular lesions and cognitive impairment has not been demonstrated.

Globally, cognitive impairment after cardiac surgery is one of the most frequent complications, particularly in aortic valve replacement (AVR). The definite cause of VCI after cardiac surgery is not known, but it could be attributed to cerebral embolic lesions due to gas particles, fat particles from the vascular wall, and calcium particles released as a result of manipulation [19]. In addition, the SENTINEL study showed that patients undergoing TAVI had a higher prevalence of cognitive impairment prior to TAVI, with a relationship between baseline cognitive function and burden of vascular lesions attributable to chronic cerebrovascular disease [20]. Therefore, VCI seen in patients with severe AS undergoing either endovascular or surgical treatment is multifactorial and involves pre-treatment as well as procedure-related and post-treatment factors. These findings underscore the importance of pre-intervention cognitive and neuroimaging tests in studies whose objective is to investigate post-surgical cognitive changes in patients with cardiovascular disease. A recent review analyzing data from studies of neurocognitive status after AVR and the differences between surgical and endovascular approaches show more consistent and favorable neurocognitive outcomes for TAVI patients, as the latest SAVR and TAVI trials have demonstrated [13, 14]. In addition, cerebral embolic protection devices offer the prospect of further improvement [21]. Nevertheless, there are several limitations to recent studies.

First, some studies use a single neuropsychological test as the primary variable for assessing changes in cognition [22–25]. In addition, only a few studies assess cognitive function in the long term [26, 27], which implies at least 6 months after the procedure. Furthermore, the definition of cognitive decline has varied from study to study, often defined simply by a decrease in mean scores in neurocognitive tests [28], and they differ with regard to the neuropsychological tests and batteries used, making it difficult for the comparability of results. Finally, it is important to consider other factors such as low educational level and medical comorbidities such as preexisting cardiovascular disease since they have been found to be risk factors for VCI [29].

Advanced imaging studies, such as resting-state MRI (rs_MRI), is used in brain mapping to assess regional interactions that occur in a negative task. Several resting-state conditions have been identified in the brain, one of which is the Default Mode Network (DMN), which is more active during the rest period than during task execution. The Salience Network (SN) is key because it regulates the activation of the Central Executive Network (CEN) while deactivating the DMN during the execution of a task. In the case of cognition, it is interesting to study the integration of these different neural networks. Interestingly, a study on VCI found differences in rs_RNM between subjects with and without cognitive impairment, which also correlate with neuropsychological tests such as the Montreal Cognitive Assessment (MoCA) [30].

In this context of uncertainty regarding the clinical importance of stroke and VCI in patients that undergo SAVR and TAVI, we designed a prospective study called ARTiCO (Aortic valve Replacement compared to Transcatheter implant and its relationship with Cognitive impairment). The specific objectives are;(1) to compare the early and late cognitive changes after the intervention in both groups;(2) to compare the occurrence of stroke during follow-up in both groups;(3) to quantify and compare the appearance of silent vascular lesions in the MRI at follow-up in both groups;(4) to study with functional MRI, changes in brain activity and functional connectivity and to correlate them with NRP functioning.

Therefore, the study aims to provide relevant information to determine whether cognitive dysfunction appears, persists, increases or even decreases and whether it does so differently between the SAVR and TAVI groups. We also will study the clinical and silent incidence of cerebral vascular disease between both techniques. Finally, we will analyze the correlation between neuropsychological and neuroimaging approaches in order to evaluate cognition.

The final goal of the study is to gather evidence that will help the Heart Team in decision-making processes regarding which treatment to apply to patients with the indication of AVR. This article describes the ARTiCO study protocol.

## Methods/design

### Aim, design and setting of the study

This is a prospective longitudinal cohort study that will include eighty non-selected consecutive subjects ranging from 70 to 85 years old with severe AS with an indication for AVR and an intermediate or high surgical risk. The participants will be evaluated by the Heart Team of a Comprehensive Center (Germans Trias i Pujol Hospital) that will assign them to SAVR, TAVI, or conservative treatment. Despite the limitation of this is not a randomized study; only those subjects who are suitable for both interventions will be included (and in many cases, the decision to undertake one treatment or another will made on the basis of availability for one or another technique). Subjects will be evaluated in three time periods: at baseline, within 1 month prior to intervention, 1 month after the intervention (early follow-up), and 1 year after the intervention (late follow-up). Throughout these periods, all study subjects will concomitantly undergo an extensive clinical examination, including neurological examination, neuropsychological evaluation, and advanced neuroimaging protocol to determine clinical and silent stroke events and cognitive status. In addition, we will study the correlation between neuropsychological and neuroimaging findings.

### Subject selection

This study will be carried out at the Germans Trias I Pujol University Hospital, a public health tertiary center of Catalonia. The advanced neuroimaging will be performed in the Comparative Medicine and Bioimage Center of Catalonia (CMCiB), a referent technological image equipment of the Germans Trias I Pujol Research Institute. The protocol has been approved by the Ethics Committee of our Institution.

The Heart Team of our hospital evaluates patients with a diagnosis of severe AS from an area of influence of approximately 600,000 inhabitants from both a rural and urban population. About 12,000 meet the diagnosis of severe AS, and 360 is the number of patients per year treated in our hospital with SAVR or TAVI. Taking into account that approximately 50% of these 360 patients underwent non-elective treatment, the number of screening candidates for the ARTiCO study screening is about 180 patients per year.

Once patients are assigned to a treatment, the Cardiac Surgeon in the case of SAVR or the Cardiologist in the case of TAVI will verify that they meet all of the following inclusion criteria. The inclusion criteria are: (1) age range from 70 to 85 years old; (2) diagnosis of a severe/symptomatic AS with an indication for elective AVR; (3) an intermediate or high surgical risk evaluated by the EuroScore II (3-10%); and (4) subjects must be eligible to be treated with both techniques. Subjects will be excluded if they have: (1) contraindications for MRI, (2) severe renal failure, (3) severe disability or previous chronic neurologic or/psychiatric disease, (4) diagnosis of dementia or Mini-Mental State Examination (MMSE) (MEC de Lobo Spanish version) <19/35 corrected for age and education [31], (5) those with previous cardiac surgery, (6) patients with severe preoperative comorbidities that may difficult a 1-year complete follow-up, (7) aortic surgery concomitant to that of AVR or other than coronary revascularization. Excluded patients will be registered for quality control in the selection of study patients. All subjects who meet all the inclusion criteria and none of the exclusion criteria will be invited to participate in the study. If they accept, they will sign the informed consent form. (Figure 1)

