Along with the neuropsychological study, which is the goal standard in the diagnosis of cognitive impairment, including VCI, neuroimaging with MRI is key to objectifying the lesions that are probably the origin of alterations in cognitive domains. In addition, functional MRI will allow us to study pathways and brain functions, as well as establish the correlation between the findings with the results of the neuropsychological study. The potential usefulness that can be obtained with the data from our study could mean using neuroimaging as an alternative to the neuropsychological study in those patients with cognitive alterations or with language alterations, such as aphasia, or of the senses such as hearing or sight, that do not allow the administration of all or some neuropsychological tests.

Strengths of this study are: 1). Although patients will not be randomized between SAVR and TAVI, they are eligible for inclusion in the study only if they are suitable for both techniques; therefore the groups will be comparable; 2). To the best of our knowledge, this is the first study that simultaneously uses an extensive neuropsychological study, with a battery designed to evaluate all domains likely to be affected in the VCI, and an advanced MRI study, with sequences to assess structural damage as well as a functional MRI to compare SAVR and TAVI in patients with severe aortic stenosis; 3). In addition, these studies will be carried out pre-treatment, in the early phase and in the late phase; 4). and will have the participation of a vascular neurologist who will evaluate the patients and the clinical events that they may present following the recommendations of the NeuroARC.

We hope that all the information obtained from ARTiCO study will contribute to a better understanding of the changes that occur in neurocognition after the two distinct types of treatment available for severe AS and therefore, that it helps Heart Teams in decision-making.

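### Suitability for both techniques is verified after treatment assignment, by a different specialist in each arm, so the design does not secure the comparability inferred from it

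*Protocol article*

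**What the plan says.** Under Aim, design and setting of the study, the Heart Team evaluates each patient and is the body "that will assign them to SAVR, TAVI, or conservative treatment". The article acknowledges that this is not a randomised study. Against that limitation it sets the restriction to patients suitable for both interventions, and adds that "in many cases, the decision to undertake one treatment or another will made on the basis of availability".

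Under Subject selection, the check of the inclusion criteria comes after that decision: "Once patients are assigned to a treatment, the Cardiac Surgeon in the case of SAVR or the Cardiologist in the case of TAVI will verify" the inclusion criteria. The fourth of these reads "subjects must be eligible to be treated with both techniques". The exclusion criteria follow, without a named assessor. On the patients who fail, the article says: "Excluded patients will be registered for quality control in the selection of study patients".

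The Discussion lists as the study's first strength that, although patients are not randomised, "they are eligible for inclusion in the study only if they are suitable for both techniques; therefore the groups will be comparable".

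**The concern.** Dual suitability carries much of the argument that the two arms can be compared, and it is a clinical judgement with no threshold in the text. For a SAVR patient, the open question is whether TAVI was also possible. For a TAVI patient, it is whether surgery was also possible. As written, the surgeon verifies the first and the cardiologist the second. Each knows the assignment, and each is asked about the technique that the other specialty delivers.

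If the two specialists draw the line differently, one written criterion becomes two filters, and the arms can differ at entry on features that also bear on cognitive change. Such a difference arises before any outcome is measured. The study's stated purpose is to inform Heart Team decisions, so a difference due to selection could be read as a difference between techniques.

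**Working it through.** **Step 1. Sequence and assessors.** Setting the sections side by side:

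| Step | Who | Source |
|---|---|---|
| Evaluation and assignment | Heart Team | Aim, design and setting |
| Verification of inclusion criteria, including dual suitability | Surgeon (SAVR) or cardiologist (TAVI) | Subject selection |
| Invitation and consent | Patients who meet all criteria | Subject selection |
| Inference that the groups are comparable | - | Discussion, strengths |

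Nothing in the article describes a record of dual suitability made by both specialties before the second step.

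**Step 2. Which criteria depend on the assessor.** Age 70 to 85 and EuroScore II 3-10% should give the same answer whoever checks them. Among the inclusion criteria, the concern falls mainly on dual suitability.

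**Step 3. Does comparability follow even with a perfect filter?** No. Availability decides in many cases, not all. The remaining choices have another basis, which is not stated, and the baseline data list does not include the reason for the choice. Patients who are all suitable for both techniques can still differ in prognosis between arms.

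**Step 4. The plan's own figure.** Inputs from Statistical considerations: difference 0.67, SD 1, two-sided alpha 5%, power 80%, loss 10%.
- Normal approximation: n = 2 × (1.960 + 0.842)² / 0.67² = 34.97, so 35 per group.
- With the t distribution: 35.96, so 36 per group, with power 0.8005.
- Recruitment: 36 / 0.90 = 40 per group.

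The stated 36 and 40 reproduce, and this point does not change them.

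**Step 5. What a difference between filters could do.** The documents give no size for it, so everything here is an assumption.

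First, a mixture. Let a share p of one arm be patients who would have failed the other arm's check, and let their change in the global index be d worse. The induced difference is p × d.
- 0.10 × 0.5 = 0.05 z; 0.05 / 0.67 = 7%.
- 0.20 × 0.5 = 0.10 z; 0.10 / 0.67 = 15%.

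Second, the effect of a shift b on the crude two-group test with 36 per group and SD 1. The standard error is √(2/36) = 0.236.
- Rejection rate with no true effect: Φ(−1.96 + b/0.236) + Φ(−1.96 − b/0.236).
- Power if the shift runs against a true 0.67: Φ((0.67 − b)/0.236 − 1.96).

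| Assumed shift b (SD) | Rejection rate, no true effect | Power against a true 0.67 |
|---|---|---|
| 0 | 5% | 81% |
| 0.1 | 7% | 68% |
| 0.2 | 14% | 51% |
| 0.3 | 25% | 35% |

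The mixture above reaches only the 0.1 row. The lower rows need a larger selection difference than that illustration assumes.

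**The case against.** The best reply is that the second check may only confirm an earlier judgement. The Heart Team sees every patient first, and a choice made by availability presupposes that both techniques were already thought suitable. That is a fair reading for those patients. It does not cover the others, and the article does not say that the earlier judgement is recorded. A fuller protocol may describe such a record, but the order and the assessors are stated here, not merely left out.

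There are also real protections: one written set of criteria for both arms, the same EuroScore II bounds, a register of exclusions, outcomes framed as change from baseline, and planned confounder adjustment. Baseline data include correlates of frailty and comorbidity such as EuroScore II, NYHA class, renal function, physical activity and the modified Rankin scale. These can reduce an imbalance. They cannot remove selection on a judgement that was not recorded, and the register is described as serving quality control only.

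Four stronger readings are tempting, and the documents do not support them:
- **That the same two specialists apply the exclusions**, such as "patients with severe preoperative comorbidities that may difficult a 1-year complete follow-up". The article names them for the inclusion criteria only.
- **That the MMSE cut-off is applied separately by arm.** The article does not say who applies it, and its neuropsychological assessment is done by one blinded neuropsychologist, so a common check fits the text.
- **That frail patients being steered away from surgery is a fault of the verification step.** That is confounding by indication from non-random assignment, and earlier verification would not cure it.
- **That the groups will in fact differ, or that the design gives no protection.** Neither can be shown.

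**Conclusion.** The point holds in a limited form. Dual suitability is verified after assignment by arm-specific clinicians, with no prior joint record described, so the criterion can act as two filters. The Discussion's step from dual suitability to comparable groups is therefore not secured, and the fact that availability settles only part of the choices weakens it further.

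The size and direction of any imbalance are unknown. On the illustrative assumptions the effect is modest: at the upper figure of 0.10 z, the crude test's false-positive rate would rise from 5% to about 7%. Larger effects need larger assumed shifts. The sample size is not in question. The matter is worth correcting because the remedy is cheap and a judgement made before assignment cannot be reconstructed afterwards.

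**What to change.** 1. At the existing Heart Team meeting, have both specialties record for each candidate whether the patient is suitable for both techniques, before SAVR or TAVI is chosen. The specialist's later check then confirms a documented joint judgement.
2. On the same form, record why the technique was chosen: availability or a clinical reason.
3. Use that reason in a sensitivity analysis limited to patients assigned by availability.
4. In the Discussion, replace the inference of comparability with a statement that dual eligibility reduces confounding by indication but does not remove it.

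The cost is a short form for each screened candidate, about 180 a year by the article's own estimate. The sensitivity subset will also be less precise: if a fraction f of each arm is assigned by availability, the standard error grows by a factor of 1/√f. The change alters what is recorded and when; it leaves the choice of treatment to the Heart Team.

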**Fig. 1 Fig1:**
[figure not shown]
ARTiCO study sample selection. The diagram shows the sample selection in ARTiCO study from the reference population. SAVR: surgical aortic valve replacement; TAVI: transcathether aortic valve implantation.

The sample size calculation will be based on the main study variable, the Global Cognitive Impairment Index (GCII), which has the Impairment Index or Global Cognitive Impairment Index, as a standardized normal distribution. Setting an alpha error of 5% and a beta error of 20% (80% statistical power) for a two-sided analysis and an effect size to observe defined as a minimal difference in z score of 0.67. Applying these criteria, we obtain an estimate of 36 patients per group. Taking into account a 10% loss to follow-up, we need a total sample of 80 subjects.

